**Electronic supplementary material:**

The online version of this article (10.1186/s13690-017-0252-2) contains supplementary material, which is available to authorized users.

## Background

Obesity is a chronic medical condition characterized by an accumulation of excess fat in the body that may lead to negative health consequences. It is the major contributor to some of the most prevalent chronic conditions, such as type 2 diabetes (T2D), heart and kidney diseases, metabolic syndrome, sleep apnea, and depression (National Institutes of Health, [5]; Ogden, 2007). Obesity is the fifth leading risk factor for deaths globally, making it an extremely important public health issue [6]. In 2014, a World Health Organization (WHO) report showed that more than 1.9 billion adults aged 18 years and older were overweight with over 600 million being obese (see Table 1 for obesity classification). In addition, 44% of the diabetes burden, 23% of heart disease burden, and 7–41% of certain cancer burdens are associated with overweight and obesity [10]. Around 2.8 million people die each year as a result of being overweight or obese. The majority of these deaths is premature and preventable and may apply an economic burden on the health systems [7].

**Table 1 Tab1:** World Health Organization Body Mass Index (BMI) classification for adults

	Principal cut-off points	Additional cut-off points
Underweight	<18.50	<18.50
Severe thinness	<16.00	<16.00
Moderate thinness	16.00–16.99	16.00–16.99
Mild thinness	17.00–18.49	17.00–18.49
Normal range	18.50–24.99	18.50–22.99
		23.00–24.99
Overweight	≥25.00	≥25.00
Pre-obese	25.00–29.99	25.00–27.49
		27.50–29.99
Obese	≥30.00	≥30.00
Obese class I	30.00–34.99	30.00–32.49
		32.50–34.99
Obese class II	35.00–39.99	35.00–37.49
		37.50–39.99
Obese class III	≥40.00	≥40.00

Source: Adapted from WHO, 1995, WHO, 2000 and WHO 2004

Attempts to reverse obesity through weight loss have been the focus of the attention of many, including researchers, scientists and clinicians. This has been chiefly achieved via dietary and lifestyle modification, however, when these have not been successful, surgical options have been adopted for morbidly obese patients (ASMBS). Bariatric surgery (BS) has been shown to be the most effective type of approach to achieve and sustain significant weight loss in morbidly obese people [9]. BS is defined as a group of surgical procedures performed to facilitate substantial weight loss by reducing the size of the stomach and/or limiting absorption in the small intestine (American Society for Metabolic and Bariatric Surgery [1]. It is considered a highly efficacious treatment for extreme obesity. However, bariatric surgery patients frequently report difficulty initiating and maintaining healthy behavioral changes following surgery [4]. Most Post-bariatric surgery patients are strictly placed on liquid diet during the early post-operative phase and are practically unable to consume large quantities of food in one sitting or taking solid protein within the first months, which put them at a higher risk of developing protein malnutrition [8].

Post-surgery multivitamin and high protein supplementation is important to avoid any nutrient deficiency [3]. High protein supplements are mainly rich in protein and supplemented with vitamins and minerals. These supplements in general are inexpensive, widely distributed, and commonly used by people or patients who need nutritional supplementation while recovering from an illness or post-surgery especially post-bariatric surgery [3].

Protein supplementation is an effective approach to ensuring that post-bariatric surgery patients maintain muscle mass and healthy levels of the above-mentioned nutrients and body compositions [2]. In the absence of this, the weight loss achieved by the surgery may present a systematic issue leading to higher fat percentage and lack of these important elements that are essential for the function of the human physiology. The imbalance of such essential body compositions and nutrient can also lead to pathological and irreversible conditions. The objective of the present study is to examine the effectiveness of protein supplementation in reducing the risk of developing protein malnutrition that lead to low muscle mass and low protein level, in post-bariatric surgery patients.

### Study objectives

#### Primary objective

To estimate the difference in change of muscle and fat mass between participants who received protein supplement and those who received the placebo.

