**Methods and analysis:**

The study was based at the Department of bariatric and metabolic surgery, Doha metropolitan and regional areas. It is envisaged that approximately 160 post-bariatric surgery patients will be randomized and followed up for 6 months. These will be males and females obese (BMI >35) Qatari patients between the aged 18–60 years. Subjects with renal or liver disease and those with past history of bariatric surgery will be excluded. By the completion of the trial, patients who took less than 80% of the supplement will be further excluded from the final analysis. Protein supplement (Cubitan,Protein, Nutricia, Netherlands) that contain daily intake of 20 g of protein to be taken orally 3 times a day throughout the study period. The placebo group will receive identical ampule containing zero-protein with exact instructions as per the intervention group. Body weight, muscle and fat mass, total protein, albumin, vit B12, Magnesium and Zinc will be measured at baseline and every follow up/study visit. Study variables will be compared between the 2 groups at different stages of the trial, including baseline, using Sample T-test (paired and unpaired) and the significance level will be confirmed with the 95% confidence interval with alpha error set to 0.05.

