### Sample size

The study population are bariatric patients admitted to bariatric department for surgery based on their eligibility criteria (BMI ≥ 35). All patients will be enrolled in the study prior to admission and will be given the intervention or the placebo on the first day post-surgery, depending on their randomization. A total of 160 obese Qatari adults from Bariatric and Metabolic Center in Hamad General Hospital (HGH), who fulfill HGH entry criteria for bariatric surgery, are expected to be enrolled in this experimental study.

Using the primary outcome estimates available in the published study (Schollenberger, A E et al.; 2016), body fat mass (BFM) and lean body mass (LBM) (kg) in the intervention group at baseline, 3 and 6 months (BFM baseline 78.2 ± 19.1, 3 and 6 months 59.9 ± 15) and (LBM baseline 65.2 ± 14.2, 3 and 6 months 58.2 ± 10.6) compared with Placebo group (BFM baseline 68.2 ± 12.0, 3 and 6 months 53.9 ± 11.5) and (LBM baseline 68.9 ± 13.4, 3 and 6 months 62.2 ± 11.3). Considering a 90% power and a type I error rate of 5%, the required sample size would be 130 participants (65 in each group), however, to compensate for possible dropouts, non-compliance and loss to follow-up an additional 15% to 20% will be added to the above sample size (a total of 160 participants i.e., 80 in each group). The only difference between the above study population and the population of our RCT is that the German study population were more obese (BMI between 49 and 52). Both studies looked at the effect of protein supplementation on muscle and fat mass in post-bariatric surgery patients.

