#### Measurements

Baseline measurement of body composition (fat mass and muscle mass), height and weight will be conducted on day one of the trial, using Tanita body composition instrument and other physical body measures.Baseline blood test for total protein, albumin, Vit B12, Zinc and Magnesium levels will be collected.All of the above measurements will be repeated at 1 month, 3 months and at the end of the follow up period (6 month).

*Note: All of the above measurements and the collection of blood sample is routine practice for post-bariatric surgery patient.

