#### Blood sample

Blood samples will be collected from patients in (HGH) laboratory at baseline and every month thereafter following an overnight fast. Complete blood count (CBC) will be used. Total protein, serum Albumin, zinc, magnesium and vitamin B12 will also be assessed. The laboratories of HGH are internationally accredited laboratories that follow international standards.

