#### Study timeline

All participants will be followed up for 3 and 6 months from day one of their participation. Therefore, each randomized pair will have their own follow-up dates, based on the recruitment pattern at the HGH. For example, a patient who enters the trial on the 3rd May, he or she will have the 3 months follow up date on the 3rd August and the 6th months follow up date on the 3rd November.

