## Statistical analysis

Data analyses will be performed using the statistical software SPSS package 23. The main aim is to analyze Body composition and other anthropometric changes throughout the follow up. The normality of the variables will be assessed by the Kolmogorov-Smirnov test. Non-parametric tests will be used in case of non-normal distributions of variables. Characteristics and demographics of participants will be summarized, based on the assignment of treatment or placebo, using means and standard deviations (SD) for quantitative variables. Baseline data for the two groups will be compared using two tailed independent samples t-tests and the *P* value of this difference for each variable will be provided. During the follow-up, changes in weight, body fat percentage, muscle mass, total protein level, albumin level, vit B12, Zinc and Magnesium will be compared within groups using paired t-test and between groups using independent sample t-test. In the case of non-normal distribution of variables, any two independent (unpaired) samples Student’s t test will be replaced by Mann-Whitney U test. However, in the case of Two dependent (paired) samples Student’s t test, Wilcoxon signed rank (paired samples) test will be used. A multiple linear regression model will also be conducted to adjust for age and gender will be conducted. Other fundamental confounders such as diet intake are not incorporated into the multiple binary regression model. This is primarily because post-bariatric patients within the 1st few months (early post-operative phase) are both unable and not allowed to take any solid foods and few specific liquid foods such as milk and soups are recommended to them by the dietician. All patients are trained to follow such diet. Moreover, being an RCT, it is expected that all confounders (including hidden confounders) are balanced between the 2 groups and no assessment of baseline variables such as diet, physical activity and any other biological differences between the 2 groups is required. This is consistent with the CONSORT statement for RCTs.

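### Two unranked primary outcomes, no primary time point and a contradictory body-composition schedule: the stated 5% type I error does not hold for the primary objective

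*Protocol article*

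**What the plan says.** - **Outcomes.** The Primary objective reads "To estimate the difference in change of muscle and fat mass between participants who received protein supplement and those who received the placebo". Muscle mass and fat mass stand side by side, with no order and no visit.
- **Testing.** The Abstract (Methods and analysis) says "Study variables will be compared between the 2 groups at different stages of the trial, including baseline", and that "the significance level will be confirmed with the 95% confidence interval with alpha error set to 0.05". The Statistical analysis section tests each change during follow-up with its own independent-samples t-test between groups and its own paired t-test within groups. An age- and gender-adjusted regression is added. The fat variable listed there is body fat percentage, not fat mass.
- **Sizing.** The Sample size section says "Considering a 90% power and a type I error rate of 5%, the required sample size would be 130 participants (65 in each group". It quotes both fat and lean mass, gives one value for 3 and 6 months together, and does not say which outcome or visit sets the number.
- **Schedule.** Under Measurements: "All of the above measurements will be repeated at 1 month, 3 months and at the end of the follow up period" (6 months). Under Study timeline: "All participants will be followed up for 3 and 6 months from day one of their participation". Study visits places body composition at monthly visits. Blood sample shows the same inconsistency for the secondary laboratory variables: "Blood samples will be collected from patients in (HGH) laboratory at baseline and every month thereafter".

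**The concern.** A type I error rate belongs to a decision, and this plan does not fix the decision. With two outcomes, several visits and 0.05 for each comparison, the outcome and visit that answer the objective can be chosen after the data are seen. The 5% in the sample size statement then does not describe the risk of a false claim.

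This has practical weight here. The strengths and limitations section expects the trial to supply a practice guideline. It also expects loss to follow-up beyond 3 months, so earlier and later results may differ, and no rule says which one counts.

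The paired within-group tests are a lesser matter. In the planning figures lean mass fell in both arms, so significance within each arm would say little about the supplement.

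**Working it through.** **Inputs.** Two primary outcomes (Primary objective). Alpha 0.05 per comparison (Abstract). Two visits (Study timeline), three (Measurements) or up to six (Study visits). 65 per arm, 90% power, 5% error (Sample size). Tests are taken as two-sided; the article says so only for baseline: "Baseline data for the two groups will be compared using two tailed independent samples t-tests". Correlations between visits and between outcomes are assumptions, because the article gives none.

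**Step 1: the plan's own figure.** One outcome at one visit: 1 − 0.95^1 = 5%. The stated rate is right for a single test only.

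**Step 2: any one significant result counts.** For k independent tests the family-wise error is 1 − 0.95^k. The correlated columns come from simulated two-sided z-tests under no effect (300,000 to 400,000 draws), with between-visit correlation 0.5 to 0.9 and between-outcome correlation 0.3 to 0.7.

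| Schedule read from | Tests (2 outcomes × visits) | Independent | Correlated |
|---|---|---|---|
| One fixed visit | 2 | 9.75% | 8.3–9.5% (outcome correlation only) |
| Study timeline | 4 | 18.5% | 11.6–16.9% |
| Measurements | 6 | 26.5% | 13.6–23.0% |
| Study visits | up to 12 | 46.0% | 17.5–36.4% |

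Repeated changes from a shared baseline in the same patients are correlated, so the independence column is an upper reference, not an expectation.

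**Step 3: both outcomes required.** At one fixed visit the error cannot exceed 5%. If success at any visit is allowed, the worst case is a large true effect on one outcome and none on the other. The error is then that of one outcome tested repeatedly:
- two visits: 1 − 0.95^2 = 9.75% if independent; 9.2% to 7.0% at correlation 0.5 to 0.9;
- three visits: 1 − 0.95^3 = 14.3% if independent; 12.6% to 8.4% at correlation 0.5 to 0.9.

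**Step 4: cost of controlling the error across two outcomes at one visit.** The stated 90% power at 65 per arm is taken as given. Whether the quoted means and SDs lead to 65 is a separate question.
- Power at 0.025: Φ(1.960 + 1.282 − 2.241) = Φ(1.00) ≈ 84%.
- Number per arm for 90% power: 65 × [(2.241 + 1.282)/(1.960 + 1.282)]² ≈ 77.
- Effect detectable with 90% power at 65 per arm: √(2 × (1.960 + 1.282)²/65) = 0.57 SD at 0.05; √(2 × (2.241 + 1.282)²/65) = 0.62 SD at 0.025.

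**Step 5: what the planning figures imply for ordering the outcomes.** Lean mass: 65.2 to 58.2 kg (−7.0) with the supplement, 68.9 to 62.2 kg (−6.7) with placebo. The changes differ by 0.3 kg, in the direction opposite to the hypothesis. Fat mass: 78.2 to 59.9 kg (−18.3) against 68.2 to 53.9 kg (−14.3), a difference of 4.0 kg.

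**The case against.** **No success rule is stated, so no error rate can be asserted.** This stands in part. The article never says that one significant result is enough, and its limitations section words the hypothesis jointly, as lower fat and higher muscle mass. A reader might infer that the true error is 17% to 26%, or that there are at least six primary tests. The documents do not support either. The first figure needs both an any-one-counts rule and low to moderate correlations. The second ignores the Study timeline, which gives only four tests. The joint reading does not rescue the 5%, however, because without a fixed visit it can still be exceeded (step 3).

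**Measuring at a visit is not the same as testing at it.** This is fair as to the count. The schedule sections describe measurement, and the Abstract speaks only of different stages. The number of tests is therefore undetermined, and a range is the honest answer.

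**Multiplicity is commonly left to a statistical analysis plan.** That is true of detailed testing procedures. The primary outcome and its time point are core protocol content, though. This article also states a 5% error that its own testing scheme does not deliver, and schedules that contradict each other.

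**The paired tests decide nothing.** Agreed. The objective is between groups, so these tests are only a matter of presentation.

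**Conclusion.** The concern holds in structure and, within limits, in size. The outcomes are unranked, no visit is primary, and the schedule is inconsistent, so the 5% in the sample size statement is not a property of the primary objective. If any one significant result counts, the family-wise error is about 12% to 26% for four to six tests. The lower end assumes strong correlation and the upper end independence. With monthly testing it could be higher, up to 46% for twelve independent tests. If both outcomes are required, 5% is protected only once a single visit is fixed. All figures beyond the single-test 5% rest on assumed correlations and an assumed success rule.

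**What to change.** 1. Name one primary time point, for example 6 months, the end of follow-up.
2. State the success rule for the two outcomes: Holm at overall two-sided 0.05, or both required at 0.05 each.
3. Name fat mass, not body fat percentage, as the tested primary variable, in line with the objective and the sizing. Say whether the t-test or the adjusted regression is the primary analysis.
4. Label other visits and variables as supportive, and report within-group changes descriptively.
5. Reconcile the body-composition schedule across Measurements, Study visits and Study timeline, and the blood schedule with it.

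**Cost.** The text changes are small, but the power statement must be restated. With Holm, an outcome that has to pass at 0.025 has about 84% power at 65 per arm. Restoring 90% needs about 77 per arm, which leaves little of the planned 80 per arm for dropout. If both outcomes are required and each has 90% power, joint power lies between 80% (1 − 0.1 − 0.1) and 90%. The near-zero lean-mass difference in the planning figures would also weigh heavily against that rule. For the same reason a fixed sequence with muscle mass first is not recommended: on the article's own figures it would probably block any claim on fat mass.

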#### Secondary objectives

The percentage of weight reduction in the intervention in comparison with control groupThe difference in protein level (albumin/total protein) in post-bariatric patients receiving intervention compared with control groupThe blood level changes in Vit B12, Magnesium and Zinc in the intervention group in comparison with the control groupThe differences in the above changes in relation to types of bariatric surgery

#### Study hypothesis

Protein supplementation in Qatari post-bariatric patients may improve or prevent the imbalance in the body’s essential proteins and nutrients and avoid muscle wasting and other undesirable health conditions.

## Methods and design

This study is a double-blinded randomized control trial where both investigators and participants will be blinded to the treatment (intervention and placebo products are identical and unlabeled). The researchers will recruit participants early 2017. The randomization will be done on a weekly basis within blocks of 8 or 10 patients. This is roughly the number of patients available per week. A simple randomization process will be employed to assign patients to either groups- intervention & placebo. Using a computer generated random list, the treatment and the placebo will be allocated in a random manner to numbers that label individual patients. For the blinding, a dietician will assign the treatment and the control to patients as per the randomization results.

Both the intervention and control groups will receive standard dietary instructions in post-bariatric surgery period including hospital stay (1–2 days) and every month thereafter. The intervention group will receive protein supplement and the placebo group zero-protein supplement everyday over the study period (6 months). The placebo & the protein supplement slightly differ in the caloric content (the difference is 150 kcal/bottle). Although this difference is not clinically significant, particularly for the early post-operative phase, this issue will be addressed as a limitation for this study.

Investigators and researchers, including providers of care (rehab staff) in this study will be blinded to the intervention, i.e. they will not be aware of who is on protein supplement and who is on placebo. Patients will also be blinded to the intervention, i.e. they will not be aware whether they are taking protein or zero protein supplement. This dietitian is also responsible for filling the intervention & control ready-to-feed shakes into identical bottles labeled either A or B. The dietician will not have any other responsibility such as data entry or follow up of participants, as this will be done by the PI and research team. Un-blinding will be unlikely within the settings of our trial, however, any suspicion of un-blinding will be dealt with appropriately and may result into the cessation of participation in the trial.

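### Patients are randomised in weekly blocks but no between-group analysis uses the block; if arms are balanced within blocks and weeks differ, the t-test is mildly conservative and some precision is lost

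*Protocol article*

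**What the plan says.** On allocation, the Methods and design section says "The randomization will be done on a weekly basis within blocks of 8 or 10 patients", and explains the block size by patient supply: "This is roughly the number of patients available per week". The next sentence reads "A simple randomization process will be employed to assign patients to either groups- intervention & placebo". The section does not say that the arms are balanced within a block.

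On analysis, the Statistical analysis section says that changes in each outcome "will be compared within groups using paired t-test and between groups using independent sample t-test". If a variable is not normally distributed, "any two independent (unpaired) samples Student’s t test will be replaced by Mann-Whitney U test". It adds: "A multiple linear regression model will also be conducted to adjust for age and gender". Neither block nor recruitment week appears in any of these.

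**The concern.** When allocation is balanced within blocks, each block contributes equally to both arms. Anything shared by the patients of one week then cancels from the difference between arms. An independent t-test does not know this: it counts week-to-week variation as part of the residual spread. Its standard error is then larger than the true sampling error of the estimate, the interval is wider than it need be, and the type I error falls below the stated 5%.

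What is at stake is precision. The estimate is not biased, and false positives do not become more frequent.

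**Working it through.** **Inputs from the protocol.** N = 160 (80 per arm); blocks of 8 or 10; 5% type I error; 90% power with 65 per group before dropout. Number of blocks K: 160/8 = 20 and 160/10 = 16.

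**Input not in the protocol.** The share ρ of outcome variance that lies between weeks. I take ρ from 0 to 0.20.

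**The plan's own figure.** The protocol gives no figure on this point. Its 65 per group does not follow from the follow-up means and SDs it cites: at 90% power, two-sided, these need 105 per arm for fat mass (difference 6.0, SD 13.4) and 158 for lean mass (difference 4.0, SD 10.96). That is a separate matter and does not depend on the block. Here 65 per group serves only to set a reference effect of 0.573 SD, which has 90% power at that size.

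**Step 1: CI width under balanced blocks.** Set the total variance to 1, with n = 80 per arm, K = 20 and m = 4 patients per arm per block.

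- The variance that matters for the arm difference is 1 − ρ.
- The t-test's pooled variance has expectation (1 − ρ) + ρ(n − m)/(n − 1), where (80 − 4)/79 = 0.962.
- SE ratio = √{[(1 − ρ) + 0.962ρ]/(1 − ρ)}.
- CI width ratio = SE ratio × t(158 df)/t(139 df), using 160 − 2 = 158 and 160 − 20 − 1 = 139. The t factor is 0.9989.

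Example, ρ = 0.10: (0.900 + 0.0962)/0.900 = 1.107; its square root is 1.052; times 0.9989 gives 1.051.

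The type I errors below come from 10,000 simulated trials per setting (simulation standard error about 0.2 points).

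| Assumed ρ | CI width, t-test ÷ block-adjusted | t-test type I error, balanced blocks |
|---|---|---|
| 0 | 0.999 | 5.1% |
| 0.01 | 1.004 | 4.9% |
| 0.02 | 1.009 | 4.5% |
| 0.05 | 1.024 | 4.3% |
| 0.10 | 1.051 | 4.1% |
| 0.20 | 1.113 | 3.2% |

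Blocks of 10, or 130 patients instead of 160, change the width ratio by no more than about 0.003.

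**Step 2: the same check under simple randomisation.** The t-test's type I error stays between 4.7% and 5.3% at every ρ. Fixed block terms do harm here: the ratio of t-test to fixed-block CI width is 0.94 at ρ = 0 and 0.99 at ρ = 0.10, so the fixed-block interval is the wider one (1/0.9365 = 1.07, about 7% wider, at ρ = 0).

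**Step 3: a random intercept instead of fixed terms.** 3,000 simulated trials per setting, 20 blocks of 8, 130 of 160 patients analysed (30/160 = 18.75% lost at random), effect 0.573, REML random intercept. The simulation standard error of each power is about 0.5 points.

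| Assumed ρ | Balanced: t-test v random block, power | SE ratio | Simple: t-test v random block, power | SE ratio |
|---|---|---|---|---|
| 0 | 91.2% v 91.2% | 1.01 | 89.0% v 89.1% | 1.00 |
| 0.05 | 91.1% v 92.3% | 1.03 | 90.6% v 90.9% | 1.01 |
| 0.10 | 90.9% v 92.3% | 1.05 | 89.5% v 90.9% | 1.03 |
| 0.20 | 91.5% v 94.5% | 1.11 | 89.9% v 92.8% | 1.07 |

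The random-intercept model's type I error was 4.5% to 5.8% across settings (simulation standard error about 0.4 points). Two further balanced-block simulations of 4,000 trials per setting agree: 89.9% v 90.2% and 90.0% v 90.2% at ρ = 0, and 92.1% v 95.0% and 91.2% v 94.4% at ρ = 0.20.

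**The case against.** A reader might infer that the reported intervals will be too wide and that the analysis contradicts the randomisation. The document does not establish either. Both need arms balanced within blocks, yet the same section also describes simple randomisation, and the Study timeline section speaks of randomised pairs. Under simple allocation the t-test is exact enough, and adjusting for week is optional covariate adjustment for precision. Both inferences also need real differences between weeks. The protocol reports none and describes one hospital, one body-composition device with prior reliability testing, and one central laboratory. A small share is therefore plausible, and the loss would be a percent or two of CI width. All of this stands, and it is why the point is conditional and minor.

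A reader might also infer a validity error. That fails too: where the t-test departs from 5%, it departs downwards.

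It can further be said that a block term is the kind of detail an article leaves to the SAP. That carries less weight here, because the article itself names the tests and the two adjustment covariates. The choice is stated, not left open.

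Finally, the block size only roughly matches weekly supply, so block and calendar week may not coincide. That is a fair caution about which variable to use.

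**Conclusion.** The point holds as a minor matter of efficiency and design-matching. No planned between-group analysis uses the blocks within which patients are to be randomised. Given balanced blocks and week-to-week variation, the t-test's CI is about 0.4% to 2.4% too wide at assumed shares of 0.01 to 0.05, about 5% at 0.10 and about 11% at 0.20, with type I error of about 4% and 3% at the last two. With no variation between weeks, or with simple randomisation, the t-test keeps its nominal level and nothing needs correcting. The size therefore rests on an assumed share and on a reading of the allocation that the protocol leaves unsettled. The recommendation does not depend on settling it, because the random intercept cost no measurable power under either reading.

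**What to change.** In the Statistical analysis section, state that the between-group estimate and 95% CI for each outcome come from the regression model with randomisation block as a random intercept, for example through the MIXED procedure of SPSS, the software already named. Use one random term, not 16 to 20 fixed terms, since fixed terms widen the interval under simple allocation at shares up to 0.10. Take the block from the randomisation list rather than inferring it from the calendar.

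The cost is one sentence and slightly more analysis work. No new patients or measurements are needed. In simulation there was no power loss when weeks do not differ, and some gain when they do.

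### Bottles carry only the code A or B, so one correct letter-to-product link could expose up to all 160 allocations; allocation is also described both as blocked and as simple

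*Protocol article*

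**What the plan says.** All but one of the statements below come from Methods and design in the protocol article.

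- **Blinding.** It is justified by the statement that "intervention and placebo products are identical and unlabeled". Of the investigators, researchers and care providers it says that "they will not be aware of who is on protein supplement and who is on placebo".
- **Bottle code.** One dietitian, who has no data-entry or follow-up role, assigns the products and fills them into "identical bottles labeled either A or B". No other bottle code is described, and no change in the meaning of the letters over time.
- **Random list.** It works with individual numbers: "the treatment and the placebo will be allocated in a random manner to numbers that label individual patients".
- **Allocation method.** First: "The randomization will be done on a weekly basis within blocks of 8 or 10 patients". Shortly afterwards: "A simple randomization process will be employed to assign patients to either groups- intervention & placebo".
- **Study timeline section.** It uses a further expression: "each randomized pair will have their own follow-up dates".

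**The concern.** A code with two values, shared by everyone in an arm, has a single point of failure. Once someone correctly ties one letter to one product, every patient whose letter that person knows is unblinded. Even without the key, a person who sees two patients' letters knows whether they share an arm.

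The article makes such a link plausible. The Materials section calls the protein supplement a familiar option at the hospital. The contents differ (20 g protein and 250 kcal against 0 g protein, fat free, 100 kcal), and patients use the bottles daily for 6 months.

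What is at stake is mainly the analysis set. Strengths and limitations concedes that product use is not measured objectively. Yet the Abstract and the Exclusion criteria remove patients who took less than 80% of their product. Knowledge of the arm could therefore influence reported intake, and so who is analysed. The stated safeguard, possible cessation of participation when un-blinding is suspected, works patient by patient and cannot contain a breach shared by everyone with the same letter.

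Separately, a reader cannot tell which allocation procedure will be run, and the two that are described behave differently in balance and in predictability.

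**Working it through.** **Inputs.** Total 160, 80 per arm, from 130 evaluable plus 15% to 20% (Sample size); block sizes 8 or 10, simple randomization and letters A or B (Methods and design).

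**1. The plan's own total.** Dividing by the retained fraction: 130/0.85 = 153 and 130/0.80 = 163. Adding a percentage: 130 × 1.15 = 150 and 130 × 1.20 = 156. The stated 160 implies a loss of 1 − 130/160 = 18.75%, inside the stated allowance. The total of 160, at 1:1, is used below.

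**2. Reach of one disclosed code.**

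| Bottle code | Patients identified by one link |
|---|---|
| Two letters, fixed meaning throughout | up to 160 of 160 (100%) |
| Letters re-keyed for each weekly block | 8 or 10 of 160 (5.0% or 6.3%) |
| Unique patient code | 1 of 160 (0.6%) |

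These figures give the reach of a breach, not its probability.

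**3. If allocation is simple.** The size of one arm is binomial with n = 160 and p = 0.5.

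- SD = √(160 × 0.5 × 0.5) = √40 = 6.3.
- 95% range = 80 ± 1.96 × 6.32 = 67.6 to 92.4, or about 68 to 92.
- A weekly group would split evenly with probability C(8,4)/2⁸ = 70/256 = 27.3% (size 8) or C(10,5)/2¹⁰ = 252/1024 = 24.6% (size 10).
- No assignment can be deduced from earlier ones.

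**4. If allocation is blocked.** Suppose each block is balanced 1:1, patients are assigned one at a time, and earlier letters are known. In a block of 2m, the expected number of final assignments that are fully determined is 2m/(m + 1).

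- Block of 8 (m = 4): 8/5 = 1.60 per block, 20.0%; over 160/8 = 20 blocks, 32 patients.
- Block of 10 (m = 5): 10/6 = 1.67 per block, 16.7%; over 160/10 = 16 blocks, about 27 patients.

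Full enumeration of all balanced blocks of each size gives the same averages.

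Steps 3 and 4 are alternatives. Only one of them can apply, and the article does not say which.

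**The case against.** Several points on the other side are sound.

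- **Unlabeled.** The word is used of the products, while A or B is put on the bottles. The likely meaning is that no product label shows. This is loose wording that needs clarifying, not a serious contradiction.
- **Fixed letters.** The article never says that A and B keep their meaning for the whole trial. That is an inference, though the natural one, since neither re-keying nor another bottle code is described.
- **Who sees the letters.** A reader might infer that blinded staff see them, because they telephone weekly about bottles. The documents do not support this: the calls and diary concern quantities taken or left, and nothing says that bottles are shown or letters recorded. The dietitian who fills and assigns is kept out of follow-up.
- **A taste, side effect or laboratory value.** A reader might infer that one of these would unblind the trial. It gives only a guess about one patient. The guess must also be right, be tied to a letter, and reach someone who knows other patients' letters. A patient can guess from taste just as well with a unique code.
- **Predictability.** A reader might infer that weekly blocks make part of the sequence deducible. None of the three conditions in step 4 is stated. Randomizing on a weekly basis also fits a batch assigned together, with no sequence to predict. Patients are enrolled before admission, which limits selective enrolment.
- **Pair.** This is a loose phrase in a paragraph about follow-up dates, not a third allocation method.
- **Unequal arms.** A 68/92 split keeps 4 × 0.425 × 0.575 = 97.8% of the efficiency of equal arms, so the loss of precision is small.

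Two things survive: the reach of the two-letter code, and the conflict between blocked and simple allocation. Neither is a gap that a fuller document would fill, because the article itself states the code and both methods.

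**Conclusion.** The point holds in a limited form. As described, the bottle code lets one correct letter-to-product link identify every patient whose letter is known, up to 160 of 160 instead of 1 of 160. This assumes that the letters keep one meaning throughout and that bottles carry no other code. The likelihood of such a link cannot be estimated from the article, but the confidence that un-blinding is unlikely is not earned by this scheme. The main consequence runs through the self-reported 80% rule. The body-composition and laboratory outcomes are instrument readings, and no bias in measuring them is claimed.

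The allocation text contradicts itself and must be reconciled whatever is done about the code. The 17% to 20% deducible share is conditional on all three requirements in step 4 and should not be read as a property of the trial as written.

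**What to change.** - **Bottle code.** Replace A and B with the unique patient numbers already on the computer-generated list. Let only the dispensing dietitian hold the key. Reword the blinding sentence so that unlabeled clearly means that no product label is visible. This does not stop a patient from guessing their own product; it stops a correct guess from spreading to others.
- **Allocation.** State one method. If it is blocked, generate the list in advance with randomly varied block sizes and state that blocks are balanced. If it is simple, remove the reference to blocks and present 80 per arm as an expected number, not a fixed one.
- **Study timeline.** Replace pair with patient, since follow-up dates run from each patient's own entry.

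The cost is individual labels in place of two letters, slightly more work for the dispensing dietitian, and a short correction to the text. The sample size and the analysis do not change.
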